	**Secondary outcome measures**									
		Participation (PROMIS short form Social Roles)		X		X	X	X		X
		Self-rated health (EuroQol-5D-3L)		X			X	X	X	X
		Return to work (Return to work questionnaire)				X	X	X	X	X
		Physical activity (IPAQ^c^)		X			X	X	X	
		Recovery (RI-5^d^)		X		X	X	X		
		Pain intensity (VAS^e^)				X	X	X		
		Patient satisfaction (Satisfaction questionnaire)							X	

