### Allocation

After inclusion, patients will be asked to complete the first online questionnaire (T_0_) within the month before surgery. After patients have completed the questionnaire, randomization will take place by means of a computer-based randomization list stratified regarding hospital, sex, and surgical procedure using permuted blocks, size 2. Patients are randomized to the intervention or the control group in a 1:1 ratio. The researcher performing randomization is independent from the recruitment or data analyses.

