### Data Analyses

#### Effect Analyses

All analyses will be performed in SPSS (IBM Corp). Baseline characteristics will be summarized using descriptive statistics and compared between the intervention and control group using *t* tests, Mann-Whitney U tests, chi-square tests, or Fisher exact tests. Survival analysis will be used to analyze time until RNA data. Both crude and adjusted analyses will be performed. Hospital, surgical procedure, and sex will be taken into account as covariates in the adjusted analyses because these are the factors for which stratification will apply. In addition, when there are clinically relevant differences between the intervention and the control group in the baseline characteristics or potential confounding factors, this will also be considered as a covariate in further analyses. To describe the distribution of the duration until RNA in both groups, the Kaplan-Meier method will be used. The Cox proportional hazard model will be applied to calculate HRs. Differences in secondary outcomes between the groups will be assessed by mixed models and multilevel logistic regression models for outcomes that are measured more than once during follow-up, and *t* tests, Mann-Whitney U tests, chi-square tests, or Fisher exact tests will be used when differences on 1 time point will be compared. Statistical analyses will be performed according to intention-to-treat principle, which will be compared to per-protocol analyses. Patients will be included in the per-protocol analyses when they used the intervention as intended, which will be defined as the generation of a convalescence plan on the website. This will be measured by a web log. Subgroup analyses will be performed regarding the surgical procedure (1. Cholecystectomy, 2. Hernia inguinal surgery and 3. Adnexal surgery) and type of surgery (gynecological vs surgical procedures). A post hoc analysis will be carried out on patients without major complications (definition described in Potential Confounding Factors).

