### Strengths and Limitations

In the earlier studies performed by our research group, the effect of the eHealth intervention was evaluated in terms of duration until RTW [16,46]. The reason the primary outcome measure in this study is changed to duration until RNA is that in the earlier studies only employed patients could participate; we believe that unemployed patients can also benefit from this eHealth care program to facilitate recovery. However, one of the reasons for chosing duration until RTW in the earlier performed studies was that this outcome measure was relatively easy to measure and objectify. Duration until RNA is more difficult to measure and objectify. Most studies using this outcome measure make use of fixed measurement instruments, which may contain questions not always applicable to all patients or may not represent the most relevant problems for patients. As far as we know, this is the first study in which RNA after surgery is measured by a measurement instrument tailored to the patient. A tailored instrument increases the validity and reliability of the primary outcome measure. The ultimate form of tailoring is computer-adaptive testing (CAT), in which after the first item, the selection of items is determined by the person’s responses to previous items. For example, Zanocco et al [47] used CAT to measure changes in patient-reported health before and after parathyroidectomy. PROMIS short forms and CATs are increasingly used as outcome measures across clinical studies in different fields [48]. In our study we will use individualized short forms because CAT software for use in the Netherlands is still under development [49]. Another strength of this study is that we developed a nonintervention (standard) website, which enables us to blind the patients to which group they are assigned. Blinding of the health care professionals, however, was not possible. But in our opinion this will not influence the study results, since the health care professionals do not play a substantial role in the intervention or of the data-collecting process. This study is also strengthened by the fact that state-of-the-art statistical methods, such as multiple imputation, bootstrapping, and multilevel analyses, will be used. A limitation of the study is the heterogeneity of surgical procedures. However, the Delphi study that we performed to compose the convalescence recommendations used in this study showed more or less the same convalescence recommendations for all surgical procedures, which suggests that the recovery periods of these surgical procedures are comparable [24,25]. In addition, the heterogeneity can be considered an advantage, because the results will be applicable to a broader population. Another limitation may be that the study is carried out in 7 hospitals, which means that the usual care that the control group receives can vary between hospitals. We tried to reduce this bias by stratifying the randomization by hospital. Finally, the baseline measurement with the activity tracker will be performed in the week before surgery and therefore cannot assure that the baseline measurement will give a representative view of the normal activity pattern of the patients. However, the patients who participate in the study will undergo elective surgery. This in general will mean that the patients will not be suffering from an acute illness or bedridden at the time of surgery. Although we cannot entirely rule out that the baseline measurement will be influenced, we nevertheless believe that the risk will be minimal.

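### The single-time-point secondary outcome (patient satisfaction) is tested without the randomisation strata, which is valid but mildly conservative if the strata predict it; low priority

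*Protocol article*

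**What the plan says.** Under Allocation, the article describes a "computer-based randomization list stratified regarding hospital, sex, and surgical procedure using permuted blocks, size 2", and adds: "Patients are randomized to the intervention or the control group in a 1:1 ratio".

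Under Effect Analyses, directly after survival analysis is named for time to return to normal activities (RNA), it says: "Both crude and adjusted analyses will be performed". It continues (final word of the sentence left out here): "Hospital, surgical procedure, and sex will be taken into account as covariates in the adjusted analyses because these are the factors for which stratification will". The Kaplan-Meier and Cox methods follow.

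Secondary outcomes come next and are split by how often they are measured. Repeated ones get "mixed models and multilevel logistic regression models for outcomes that are measured more than once during follow-up". For the others, t tests are named and then "Mann-Whitney U tests, chi-square tests, or Fisher exact tests will be used when differences on 1 time point will be compared". No adjusted or stratified counterpart is given for this second group.

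In Table 2 the row "Patient satisfaction (Satisfaction questionnaire)" has one mark, at 3 months. The other rows in the secondary-outcome block are all measured more than once after surgery.

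Under Strengths and Limitations the article grants that "the usual care that the control group receives can vary between hospitals".

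**The concern.** The reason given for adjusting, that these are the stratification factors, is not peculiar to RNA. It applies to any comparison of the arms. With permuted blocks of 2, the arms are nearly equal in number within each hospital, sex and procedure cell, so differences between cells contribute almost nothing to the difference between arms. A two-sample test still leaves those differences in its error term. If the cells differ in satisfaction, the standard error is too large, the real significance level falls below the nominal 5%, and power is given away.

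Some dependence on hospital is plausible. The questionnaire covers satisfaction with perioperative care in both groups, and the article says that usual care may differ between hospitals. Satisfaction is also one of the outcomes in which patients could register the replacement of the standard outpatient visit, so it deserves an efficient comparison with an effect size and interval. A bare Mann-Whitney, chi-square or Fisher p-value supplies no stratum-adjusted effect size.

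**Working it through.** **The plan's own figure.** The only power statement concerns the primary outcome: 285 events and 308 patients for a hazard ratio of 1.4, two-sided 5%, 80% power.
- Freedman: (2.4/0.4)² × (1.960 + 0.842)² = 36 × 7.849, giving 283 events.
- Schoenfeld: 4 × 7.849 / (ln 1.4)², giving 278 events.
- Total: 285 / (0.975 × 0.95) = 307.7, giving 308 patients.

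The stated figures are reproduced to within 3%. No power figure is given for satisfaction, so there is nothing to contradict there.

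**Inputs for the check.**
- 308 patients less 5% dropout = 293, or 146.5 per arm (Sample Size Calculation).
- Two-sided 5% level.
- Outcome SD set to 1.
- R² = share of the outcome variance explained by the strata. The documents give none, so 0, 5%, 10% and 20% are assumed.

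**Formulas (normal approximation, full balance within strata).**
- SE reported by the unadjusted test: √(2/146.5) = 0.117.
- True SE under stratified allocation: 0.117 × √(1 − R²).
- Excess CI width: 1/√(1 − R²) − 1.
- True size: 2 × [1 − Φ(1.96/√(1 − R²))].
- Power A. The difference is fixed at (1.960 + 0.842) × 0.117 = 0.327 SD, which gives 80% power when R² = 0. Unadjusted power is Φ(0.842/√(1 − R²)). Adjusted power is Φ(2.80/√(1 − R²) − 1.96).
- Power B. The difference is set so that the adjusted analysis has 80% power. Unadjusted power is 1 − Φ(1.96/√(1 − R²) − 2.80).

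For example, at R² = 10%, √0.90 = 0.949. The CI is 1/0.949 = 1.054 times as wide. The true size is 2 × [1 − Φ(2.066)] = 3.9%.

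| Assumed R² | True size | CI too wide by | Power A: unadjusted / adjusted | Power B: unadjusted (adjusted 80%) | Points lost (A, B) |
|---|---|---|---|---|---|
| 0 | 5.0% | 0% | 80.0% / 80.0% | 80.0% | 0, 0 |
| 5% | 4.4% | 2.6% | 80.6% / 82.0% | 78.5% | 1.4, 1.5 |
| 10% | 3.9% | 5.4% | 81.3% / 84.0% | 76.9% | 2.7, 3.1 |
| 20% | 2.8% | 11.8% | 82.7% / 87.9% | 72.9% | 5.2, 7.1 |

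**Simulation check.** The setting was 35 strata (7 hospitals × 5 possible sex-procedure cells, adnexal surgery being confined to women), blocks of 2, incomplete blocks, 5% dropout and 2,000 runs per setting. The adjusted analysis used a fixed effect for every stratum.

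| Assumed R² | Size: t / Mann-Whitney / adjusted | Power: t / adjusted | Mean SE ratio, unadjusted to adjusted |
|---|---|---|---|
| 0 | 6.3% / 5.7% / 6.0% | 78.8% / 78.3% | 0.99 |
| 5% | 4.7% / 5.0% / 5.3% | 80.6% / 81.1% | 1.015 |
| 10% | 3.7% / 3.7% / 4.7% | 81.2% / 83.8% | 1.04 |
| 20% | 2.7% / 2.8% / 4.9% | 83.3% / 88.0% | 1.10 |

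The t test is exact at R² = 0 in this setting, so its 6.3% there is simulation error (standard error about 0.5 point). The simulated sizes should be read to within about a point. The direction is clear from 10% upwards. The SE ratios are slightly below the formula values (1.026, 1.054 and 1.118), because blocks are incomplete, patients drop out, and 35 stratum effects must be estimated.

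**The case against.** The strongest reply is that nothing here is an error. A two-sample test with a true size of 2.8% to 4.4% never exceeds its nominal level and biases no estimate. That stands: a reader might infer that the tests are invalid or produce false positives, and neither the documents nor the arithmetic support it.

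A second reply is that the sentence promising crude and adjusted analyses is not expressly limited to RNA, so the simple tests may be only the crude half. That reading is possible. But the sentence lies between the RNA survival analysis and the Kaplan-Meier and Cox methods, and no adjusted method is named for single-time-point outcomes. The text is at best unclear, and the same added sentence would resolve it. Nor is this merely detail left to an analysis plan, since the article itself names the tests.

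Third, the reach is small. The outcome is one self-developed questionnaire, its app and activity-tracker parts apply to the intervention group only, and the trial is not powered on it. This also stands.

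Fourth, every size quoted depends on an assumed R². The article says that usual care can vary by hospital, not that satisfaction does, and it regards recovery after the procedures as comparable. Nothing in it supports 20% over 0. This stands too.

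Fifth, the CI-width figures concern mean differences. A logistic or ordinal model estimates a conditional odds ratio, whose standard error on the log scale typically rises with adjustment. This is correct and limits what can be claimed.

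Finally, a reader might infer that the choice of test makes it easier to present the substitution of care as harmless. The documents state no equivalence or non-inferiority claim on satisfaction, so that goes too far.

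**Conclusion.** The point holds as a modest matter of efficiency. The plan stratifies on three factors, adjusts for them alongside RNA, and then names covariate-free tests for the single-time-point secondary outcome. The cost is a conservative test: nothing at R² = 0, about 1.5 points of power at 5%, about 3 at 10%, and 5 to 7 at 20%. The interval widths in the table are upper figures, because incomplete blocks and dropout reduce them slightly. All of this rests on an assumed R² and on a score analysed as a mean difference. Mann-Whitney tests lose size in the same way in the simulation. Chi-square and Fisher tests were not simulated.

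The primary outcome, the repeated secondary outcomes and the economic evaluation are unaffected. Priority is low.

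**What to change.** Add one sentence to Effect Analyses stating that the adjusted analyses also cover between-arm outcomes measured at a single time point, and name the method by type of outcome:

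- Scores: linear regression on arm plus hospital, sex and surgical procedure, reporting the adjusted difference with its 95% CI.
- Ordered or categorical items: a stratified test (van Elteren or Cochran-Mantel-Haenszel), or an ordinal or logistic model with the same covariates. Note that its odds ratio is conditional and that the gain in CI width does not carry over to it.
- Sparse counts: keep the Fisher exact test.

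This needs no patients, no new data and no change to the questionnaires. The article reports that analyses had not begun when it was submitted, so from that position the choice can be fixed before any results are seen.

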### Interventions

#### Control Group

Patients allocated to the control group will receive usual care and access to the nonintervention part of the website (www.ikherstel.nl). On this part of the website, the patient information brochure about the surgical procedure from the hospital where the patient will have surgery is presented. This is the same brochure as the one patients often receive in various hospitals when they are scheduled for surgery. The only reason to give patients access to this website is to minimize the bias in estimation of the intervention effect. Furthermore, pre- and postoperative care will be given according to the local protocol of the hospital. In the Netherlands, patients do not receive structural and detailed instructions about the resumption of normal activities including work. Usually, after the patient is discharged from the hospital, an outpatient postoperative consultation is scheduled 4 to 8 weeks following surgery.

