#### Intervention Group

Patients in the intervention group will receive access to the intervention part of the website, a mobile application, and an activity tracker. Table 1 provides an overview of the different components of the intervention.

**Table 1 table1:** Components of the intervention.

Component	Target population	Content	Aim
Website	All patients of the intervention group	Information by text and animations^a^	Enhancing patient involvement and recovery expectations and reducing anxiety
		Making a personalized convalescence plan^a^	Creating recovery expectations and improving recovery
		Recovery monitor and recovery report^a^	Reducing uncertainties and fear related to the recovery process and improving monitoring of postoperative care
		eConsult	Increasing access to care, reducing patient uncertainties and fear related to the recovery process, and reducing costs and workload (by replacing the appointment in the outpatient clinic)
App	All patients of the intervention group with a smartphone	Information by text^a^	Enhancing patient involvement and recovery expectations and reducing anxiety
		Insight in the convalescence plan^a^	Creating recovery expectations and improving recovery
		Recovery monitor and recovery report^a^	Reducing uncertainties and fear related to the recovery process and improving monitoring and transition of postoperative care
		Creating a packing list	Helpful tool
		Section to make notes	Helpful tool
Activity tracker	All patients of the intervention group with a smartphone which can be linked to an activity tracker	Monitoring and giving feedback on recovery^a^	Reducing uncertainties and fear related to the recovery process, which may improve recovery

^a^Content is based on the intervention mapping study of Vonk Noordegraaf et al [14].

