###### Making a Personalized Convalescence Plan

The most important tool on the website is the option to generate a personalized and tailored convalescence plan, including advice about resumption of daily (work) activities (Figures 2 and 3). Using a modified Delphi method, specific convalescence recommendations were developed for several types of abdominal surgical procedures [24,25]. The recommendations given are tailored to the patient and are based on the input of patients’ normal preoperative activities and the surgical technique (using algorithms). It aims to improve recovery, return to normal (work) activities, and quality of life. The convalescence plan will be approved electronically on the first postoperative day by the operating surgeon, resulting in a definitive convalescence plan. If complications occur during surgery, the surgeon will not approve the convalescence plan and the patient will receive a message that their initial convalescence plan is no longer applicable and that the adjusted instructions of the surgeon should be followed.

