#### Process Measures

A process evaluation of the intervention will be carried out in accordance with the Linnan and Steckler method [39]. Table 3 contains the different components of the intervention and the level at which they are measured and in what way.

**Table 3 table3:** Process evaluation.

	Website	App	eConsult	Telephone consult after 2 weeks	Activity tracker
Reach: The proportion of intended target audience that participated in the study	Patients who met the inclusion criteria, signed informed consent, and are randomized to the intervention or control group^a^						
Dose delivered: The number or amount of intended units of each component delivered or provided to the intervention group	Proportion of the patients of the intervention group who received an account for the web portal and app^a^			Proportion of the patients of the intervention group who received a telephonic appointment at discharge^b^	Proportion of the patients of the intervention group who received an activity tracker^a^
Dose received: The extent to which participants from the intervention group actively engage with, interact with, are receptive to, or use materials or recommend resources	Proportion of the patients of the intervention group that made a convalescence plan^c^	Proportion of the patients of the intervention group that used the app^d^	Proportion of the patients of the intervention group that asked one or more questions on the web portal^c^	Proportion of the patients of the intervention group that received their telephonic appointment^b^	Proportion of the patients of the intervention group that connected the activity tracker to their phone^c^
Fidelty: The extent to which the intervention was delivered as planned	Proportion of the convalescence plans that are electronically approved by the specialist^c^	X	Proportion of the questions that were answered^c^	Proportion of the patients of the intervention group that came back at the outpatient office in addition to their telephonic consult^b^	Proportion of the patients of the intervention group that used the activity tracker in the first 3 weeks after surgery (minimum 3 days per week) and in the sixth week after surgery (minimum 3 days)^c^

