### Blinding

Patients are blinded to the intervention as they do not know which program is developed as a nonintervention or intervention care program. After allocation, patients will receive an email containing a link to the care program to which they are allocated. Both care programs can be accessed through the website, but after signing in, patients will receive access only to the part of the website to which they are randomized. The researchers involved in the analyses will be blinded to the allocation throughout the analyses. Health care providers cannot be blinded to the intervention because it is highly likely that they will be notified of the allocation either by the patient or the patient’s medical file.

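### The per-protocol criterion can be met only in the intervention arm, so the comparison set beside intention-to-treat is open to selection bias of unknown size and direction

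*Protocol article*

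**What the plan says.** The Effect Analyses section of the protocol article names two analysis populations and relates them: "Statistical analyses will be performed according to intention-to-treat principle, which will be compared to per-protocol analyses". Patients are "included in the per-protocol analyses when they used the intervention as intended, which will be defined as the generation of a convalescence plan". The data source is also fixed: "This will be measured by a web log". No criterion is given for control patients.

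Other sections show who can meet the rule:

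- Table 1 (Intervention Group) lists "Making a personalized convalescence plan" among the website components for intervention patients.
- Control Group: "Patients allocated to the control group will receive usual care and access to the nonintervention part of the website". That part holds the hospital's information brochure.
- Blinding: after signing in, "patients will receive access only to the part of the website to which they are randomized".
- Table 3 (Process Measures) counts plan-making in one arm only, as dose received: "Proportion of the patients of the intervention group that made a convalescence plan".

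The section on the convalescence plan describes making one as an option open to the patient. The surgeon approves the plan on the first day after surgery, so it is normally made before the operation and, under Allocation, after randomisation.

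**The concern.** A per-protocol rule that applies to one arm removes patients from that arm alone. Here the removal depends on something patients choose to do after randomisation. Patients who sit down before surgery to plan their recovery may differ in motivation, expectations, education or fitness from those who do not. The control arm contains both kinds and cannot be sorted in the same way. Under Providing Information About the Surgical Procedure and Recovery Process, the article itself cites expected length of recovery as an important predictor of actual length, so a link between engagement and prognosis is credible.

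What is at stake is interpretation. If the per-protocol hazard ratio exceeds the intention-to-treat one, it will be tempting to report that the program works when it is used. Selection could produce all or part of such a gap.

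**Working it through.** **1. The plan's own figures.** The article gives no number for the per-protocol set, so the only figures to reproduce are those of the sample size. For HR 1.4, two-sided 5% and 80% power, Freedman's formula gives (1.960 + 0.842)² × (2.4/0.4)² = 282.6, or 283 events. Schoenfeld's gives 4 × (1.960 + 0.842)² / (ln 1.4)² = 277.3, or 278. The stated 285 is close to both. Allowing for 2.5% without return and 5% dropout, 285/(0.975 × 0.95) = 307.7, which gives 308. The sample size stands and this point does not touch it.

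**2. Literal reading.** Controls able to generate a plan: 0 of 154. No hazard ratio can be estimated.

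**3. Plan-makers against all controls, with no treatment effect.** Two inputs are needed, and the documents give neither:

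- *u*, the share of patients who make a plan (in the control arm, who would have made one). Assumed 0.60, 0.75 and 0.90.
- *g*, the recovery hazard of plan-makers relative to the others, from prognosis alone. Assumed 0.67 to 2.0.

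With constant hazards and 1 as the hazard of the others, the control arm starts with an average hazard of *ug* + (1 − *u*). The per-protocol hazard ratio therefore starts at *g* / (*ug* + 1 − *u*). For *u* = 0.60 and *g* = 2 this is 2/(1.2 + 0.4) = 1.25. It then moves towards *g*, because the quicker patients leave the control risk set first. For *g* = 0.67 it starts at 0.67/(0.402 + 0.4) = 0.84 and drifts towards 1, because the slower plan-makers come to dominate the controls still at risk.

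A Cox model averages over follow-up. The table shows 2,000 simulated trials per cell, with 154 patients per arm, exponential times, the last 2.5% censored, a true hazard ratio of 1.0 and no covariate adjustment. The percentage is the rate of significant results in favour of the intervention (nominal 2.5%).

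| *g* | *u* = 0.60 | *u* = 0.75 | *u* = 0.90 |
|---|---|---|---|
| 0.67 | HR 0.87, 0.2% | HR 0.92, 0.2% | HR 0.97, 1.5% |
| 0.8 | HR 0.92, 0.6% | HR 0.95, 0.6% | HR 0.98, 2.0% |
| 1.0 | HR 1.00, 2.3% | HR 1.00, 2.9% | HR 1.00, 2.3% |
| 1.25 | HR 1.10, 10% | HR 1.06, 7% | HR 1.02, 4% |
| 1.5 | HR 1.19, 25% | HR 1.12, 14% | HR 1.05, 6% |
| 2.0 | HR 1.36, 62% | HR 1.22, 34% | HR 1.09, 11% |

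In the same simulated trials the intention-to-treat test rejected in 4% to 6% of cases (two-sided, nominal 5%), whatever *u* and *g*.

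**The case against.** **A control arm is plainly intended.** The per-protocol result is to be compared with intention-to-treat, and the phrase about using the intervention naturally refers to intervention patients. This is fair, and the literal reading is unlikely to be followed. But the second reading is the one with the bias, and the rule is stated outright, so this is more than detail left to a fuller document.

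**A reader might infer that the analysis will show a false benefit.** The documents do not support that. They give no rate of plan-making and no prognosis for plan-makers. The bias is nil if the two are unrelated, small if nearly everyone makes a plan, and reversed if patients who expect trouble engage more. A hazard ratio near the design value of 1.4 needs the extreme corner of the table.

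**Adjusted analyses are planned.** They cover hospital, procedure and sex, plus baseline factors with clinically relevant differences. Education, recovery expectations and the baseline PROMIS T-score are all collected (Prognostic Factors). Adjustment could remove part of the bias, so the table describes the crude analysis only. It cannot remove unmeasured motivation, and the article does not say that balance will be checked again within the per-protocol set.

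**A reader might also object to counting patients whose plan was withdrawn.** After an intraoperative complication, "the surgeon will not approve the convalescence plan and the patient will receive a message that their initial convalescence plan is no longer applicable", yet such a patient still meets the criterion. This is not a fault. Dropping complicated cases from the intervention arm while controls with complications stay would add bias in favour of the intervention.

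**Intention-to-treat governs.** This stands. It limits the consequence to a secondary comparison.

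**Conclusion.** The concern holds in a limited form. The criterion has no counterpart in the control arm, and the only workable reading gives up the protection of randomisation. The bias plausibly favours the intervention, but neither its direction nor its size can be fixed from the documents. Over the assumed ranges the unadjusted hazard ratio under no effect lies between about 0.87 and 1.36. These values rest on assumed uptake, assumed prognosis ratios and constant hazards, and they illustrate rather than predict. The primary intention-to-treat conclusion, the sample size and the economic evaluation (also intention-to-treat) are unaffected. The rule should be changed because its result is meant to be read beside the main one.

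**What to change.** 1. State that all control patients are kept in the per-protocol comparison.
2. Label plan-makers against controls as descriptive, and say that it is not evidence of efficacy when the program is used.
3. Adjust that comparison for named baseline predictors already collected: recovery expectations, education, baseline PROMIS T-score and the stratification factors. Do not leave the choice to observed imbalance.
4. Add a supportive complier-average estimate that keeps every randomised patient and uses randomisation as the instrument for having made a plan. One form is the difference between arms in restricted mean time to return to normal activities over 6 months, divided by the proportion making a plan.

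The fourth step needs an explicit caveat and should not be the only replacement. It assumes that allocation affects recovery only through the plan, which is doubtful here. Intervention patients without a plan still have eConsult and the telephone call, may have the app or tracker, and have no standard outpatient appointment. If those components shift recovery by δ in everyone and the plan adds nothing, the estimate is δ/*u*, which is 1.67δ at *u* = 0.60 and 1.11δ at *u* = 0.90. It may therefore be inflated.

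The cost is a few sentences and one short extra analysis, with a wider confidence interval than the per-protocol comparison and a measure other than the hazard ratio. No new data are needed, and the article reports that analysis had not begun when it was submitted.
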